### Statistical methods

A descriptive study of all the measured variables will contain the mean, standard deviation, minimum and maximum value and dispersion coefficient. The homogeneity of the intervention and control group at the initial moment – that is, that there are no statistically significant differences between the two groups in any of the variables measured – will be verified by performing a two-tailed test of means for independent samples for each variable (Additional file 2).

The effect of the mHealth W@W-App programme will be measured by continuous variables (Table 1) which will be used to evaluate the differences between before and after implementing the mHealth programme. In some variables, the programme will be effective if the mean increases in the intervention group while for other variables effectiveness will happen if the mean decreases. For example, the programme will be effective if physical activity increases and total cholesterol decreases. Therefore a one-tailed test of means will be performed. For these continuous variables, the difference of the variable between moment t of the measurement and the initial moment will be calculated, (*X*_*Dt*_ = *X*_*t*_ − *X*_0_), which quantifies whether there have been changes, after t months, associated with the intervention. The intervention has a positive effect if the results of the intervention group are significantly better than those of the control group; that is, if the values of the variable *X*_*Dt*_ are better in the intervention group. The qualitative variables (see Table 1) will be used to check if any patients display unusual behaviour that are due to changes in their medication or diet [86]. Intention-to treat analysis will be used. The statistical tests to be carried out in the event that homogeneity between the groups is not accepted while the procedure is outlined in Additional file 3.

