### Sample size

Using the free software G*Power [87], the sample size was calculated based on the power of the test and the effect size. Table 2 shows the results for powers of 0.95 and 0.80 and three effect sizes (i.e. small, medium and large). If the intervention and control group are homogenous, the sample size to be taken for a mean effect is 176 in total; 88 patients to the intervention group and 88 to the control group. With a total sample size of 176, the power of the homogeneity test is 0.91 (Table 2).

**Table 2 Tab2:** Power function to test homogeneity of the control and intervention group as a function of the effect size

Effect size (∆*μ* = *d* ∙ *σ*))	Power function
Small (*d* = 0.2) (*n* = 1084, power 0.91)	
Medium (*d* = 0.5) (*n* = 176 power 0.91)	
Large (*d* = 0.5) (*n* = 70 power 0.91)	

It is estimated that on average there is a loss of 20% of patients in clinical trials. If the sample size is increased by this percentage, 220 patients will have to be recruited; 110 in the intervention and 110 in the control group. If the losses do not exceed 20%, a test power of 0.95 would be guaranteed for a mean size effect. If the sample size is not increased at baseline, a loss of 20% would mean having a sample size of 140 patients, which would mean a test power of 0.90. The effect size capable of detecting the test performed with a power of 0.95 or 0.8 shows in additional file 4.

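### The default test on unadjusted change from baseline is valid, but less precise than adjusting for the baseline value the trial already collects

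*Protocol article*

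**What the plan says.** The Statistical methods section of the protocol article fixes the effectiveness analysis in three steps. For each continuous variable, "the difference of the variable between moment t of the measurement and the initial moment will be calculated". The arms are then compared on that difference: "Therefore a one-tailed test of means will be performed". The criterion is that "The intervention has a positive effect if the results of the intervention group are significantly better than those of the control group", which the section spells out as better values of the change variable. No model with the baseline value as a covariate is named.

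Before this, baseline comparability is checked by "performing a two-tailed test of means for independent samples for each variable". A separate route exists if that check fails: "The statistical tests to be carried out in the event that homogeneity between the groups is not accepted" are referred to Additional file 3, which is not shown.

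The Sample size section plans a plain comparison of two means: medium effect d = 0.5, 88 evaluable patients per arm, 220 recruited to allow for 20% loss, and power 0.95. Table 2 defines the effect as d times sigma, without saying whether sigma is the SD of the change or of a single measurement. Table 1 shows a baseline measurement for every outcome.

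**The concern.** Subtracting the baseline value removes it with a fixed slope of 1. With similar SDs at baseline and follow-up, the slope that minimises variance is rho, which is below 1 for any outcome that is not perfectly stable. A slope of 1 therefore has two consequences.

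- The estimate carries more variance than one from a model that estimates the slope (ANCOVA).
- An arm that happens to start worse is given too much credit, because part of its later improvement is regression to the mean.

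The second point has some practical weight here, because the Allocation section describes simple randomisation with nothing to balance baseline values. At stake is precision that the trial could have from data it is already collecting, across many outcomes.

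**Working it through.** **Inputs.** From the Sample size section: d = 0.5, 88 per arm, 1:1 allocation, 20% loss, power 0.95. From Statistical methods: one-tailed test of X_t − X_0. Alpha is not stated; 0.05 is assumed because it reproduces the stated figures. Rho is not given; 0.3 to 0.9 is assumed. The SD is assumed equal at baseline and follow-up.

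**Reproducing the plan.** Noncentral t, two independent means, d = 0.5:
- one-sided 5%, power 0.95: 88 per arm, 176 in total (stated 176);
- 176 / 0.80 = 220 (stated 220);
- two-sided power at 88 per arm: 0.910 (stated 0.91 for the homogeneity test);
- one-sided power at 70 per arm: 0.903 (stated 0.90 with 140 patients).

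The sample size is therefore not in error.

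**Variance.** With single-measurement variance σ²:
- change score: 2(1 − rho)σ²;
- ANCOVA (large sample): (1 − rho²)σ²;
- ratio ANCOVA / change = (1 + rho)/2, below 1 for every rho below 1.

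A simulation of 4,000 trials with 88 per arm gave ratios of 0.64, 0.74 and 0.89 at rho 0.3, 0.5 and 0.8 (formula 0.65, 0.75, 0.90). Both estimators averaged the true effect of 0.5.

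**Reading A: d = 0.5 in SDs of change.** The planned test has one-sided power 0.951 at 88 per arm. For ANCOVA the effective d is 0.5 / √((1 + rho)/2).

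| rho | variance ratio | SE excess of change score | ANCOVA power, 88 per arm | ANCOVA n per arm for 0.95 |
|---|---|---|---|---|
| 0.3 | 0.65 | 24% | 0.993 | 57 |
| 0.5 | 0.75 | 15% | 0.985 | 66 |
| 0.7 | 0.85 | 8% | 0.974 | 75 |
| 0.8 | 0.90 | 5% | 0.967 | 79 |
| 0.9 | 0.95 | 3% | 0.959 | 83 |

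**Reading B: d = 0.5 in SDs of a single measurement.** The effective d is 0.5 / √(2(1 − rho)) for the change score and 0.5 / √(1 − rho²) for ANCOVA. One-sided power at 88 per arm:

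| rho | change score | ANCOVA |
|---|---|---|
| 0.3 | 0.874 | 0.965 |
| 0.5 | 0.951 | 0.985 |
| 0.7 | 0.996 | 0.999 |

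Below rho 0.5, 2(1 − rho) exceeds 1, so the change score is less precise than comparing follow-up values and ignoring baseline (power 0.951 on this reading).

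**Chance imbalance.** The standard error of the baseline difference is √(2/88) = 0.15 SD. An imbalance of δ shifts the expected change-score difference by −(1 − rho)δ. One standard error at rho 0.5 gives 0.5 × 0.15 = 0.075 SD, or 15% of an effect of 0.5 SD.

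**The case against.** The strongest reply is that nothing here is an error. The change-score comparison answers the stated question without bias over randomisation, and the trial is sized for the test it plans. That stands, and it limits the point to efficiency. ANCOVA's advantage under a given baseline imbalance is a conditional property that relies on the linear model being adequate.

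The gain may also be small. For outcomes such as weight, BMI and waist a high rho is plausible, and at 0.8 to 0.9 on Reading A power moves only from 0.951 to 0.967 or 0.959. That stands too.

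Additional file 3 may contain a baseline-adjusted analysis. Its content is unknown, but the text reserves it for when homogeneity is not accepted. It therefore leaves the default unchanged, and using it would make the method depend on a baseline significance test.

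A reader might infer that the plan is underpowered and that adjustment is needed to restore 0.95. The documents do not support this. The stated 0.95 belongs to the one-tailed test and is met on Reading A. On Reading B the shortfall at rho 0.3 is gone at 0.5. Nor would adjustment secure 0.95 if the tests were made two-sided, which is a separate question: on Reading A, two-sided ANCOVA power is 0.983, 0.968, 0.947, 0.935 and 0.923 at rho 0.3, 0.5, 0.7, 0.8 and 0.9.

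**Conclusion.** The point holds as an efficiency recommendation. The default analysis is valid and correctly sized, but it gives up precision for any rho below 1 and is more sensitive to chance baseline imbalance than it need be. Its standard error is larger than ANCOVA's by 24% at rho 0.3, 15% at 0.5, 8% at 0.7 and 3% at 0.9. The direction does not depend on rho; the size does, and the protocol gives no value. A shortfall against the stated power arises only if d is in single-measurement SDs, which Table 2 leaves open, and rho is below about 0.5. The figures rest on alpha 0.05 one-sided, equal SDs at baseline and follow-up, and 88 evaluable patients per arm.

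**What to change.** In Statistical methods, for each truly continuous outcome, make the pre-specified main analysis a linear model of X_t (or, equivalently for the arm effect, X_t − X_0) on arm and X_0. Apply it whatever the homogeneity test shows, and report the adjusted mean difference with its 95% confidence interval. Do this at each visit where the outcome is measured: 3, 6 and 12 months in general, but 6 and 12 months only for glucose, HbA1c and the lipids, which have no 3-month measurement in Table 1.

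Some items that Table 1 labels continuous are not: the sufficiently or insufficiently active category from the SBPAAT, the work-related health problems reported as percentages, and days of sickness absence. State for these a binary or count model suited to the type. State also whether sigma in Table 2 is the SD of the change or of a single measurement.

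The cost is a few sentences of text and a small change to the analysis code. No additional data or patients are needed, and the arm effect can still be read as a difference in change.

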### Objectives

In this context, the main objective of this protocol for a randomized controlled trial is to assess the effectiveness in the short-medium and long term of a mHealth programme to “sit less and move more” at work on reducing sedentary behaviour and increasing habitual and work physical activity in office staff with DM2. The secondary objectives are to evaluate the effectiveness of the programme on i) clinical variables: glycaemic control and lipid profile; ii) anthropometric and blood pressure variables; iii) improvement in mental well-being, presenteeism, absenteeism and work-related stress.

This is important given the scarcity of studies that evaluate the effectiveness of mHealth programmes in reducing sedentary behaviour as a therapeutic approach for people with chronic pathology, specifically with DM2, which also evaluate the global health impact of the mHealth intervention on clinical parameters, mental well-being and productivity [46]. This study will make it possible to clarify whether people diagnosed with one of the most prevalent chronic diseases, DM2, are likely to benefit from the implementation of mHealth interventions by healthcare professionals in a wide range of health variables and through the use of objective measures of habitual and occupational sedentary behaviour [49].

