### Objective habitual and occupational physical activity

The activPAL3TM will be used to measure and quantify the sedentary behaviour patterns and physical activity of employees across weekdays (working and non-working time) and weekends. Working and non-working times will be established by using participants’ daily records. The activPAL3TM device is a valid measure to quantify body posture and activity patterns during free-living conditions [72]. The device will be attached to participants’ right thigh using a flexible nitrile sleeve and a transparent film (10 × 10 cm of hypoallergenic Tegaderm™ Foam Adhesive Dressing). The waterproof dressing of the activPAL3TM allows participants to wear the monitor continuously for 24 hours per day for 7 complete days. Participants will receive additional dressings and instructions on how to reattach the device if needed. Additionally, participants will be asked to record their daily wake-up time, bedtime, working hours, and any monitor removal time.

Data will be processed using activPAL Professional Software™ (version 7.2.32), Microsoft Excel 2010 (Redmond, WA, USA), and MATLAB v8.4 (MathWorks®, Natick, MA, USA), following previously published protocols [80]. Resulting from the activPAL3TM software output, the following outcomes will be determined: total sitting time, total standing time, total number of sitting bouts and number of sitting bouts with three different lengths (< 20 min, 20–40 min, 40–60 min and > 60 min). Additionally, total time spent in light-intensity physical activity and moderate-to-vigorous physical activity will be determined by using previously validated count-to-activity thresholds [81].

*Positive mental well-being.*

The Warwick-Edinburgh Mental Wellbeing Scale (WEMWBS) will assess positive mental well-being over the previous 2 weeks [75]. The 14-item scale has five response categories: 1 (“None”) to 5 (“All the time”). Responses are added to identify the final score, 14–70, and indicating low to high positive mental well-being. WEMWBS shows high internal reliability (Cronbach’s alpha = 0.93) and 1 week test-retest reliability (r = 0.97) in the Spanish population [82].

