### Data collection methods

The data collection will be carried out at the beginning and at 3, 6 and 12 months using the activPAL3TM device, data from the computerized medical history and a survey. At 6 and 12 months, each patient will have a blood test done for the clinical variables (Table 1). In each measurement, the participants will be summoned in consultation to record the subjective and objective habitual and occupational sedentary behaviour and the subjective and objective habitual and occupational level of physical activity.

**Table 1 Tab1:** Data collection methods for the Walk@Work-App study protocol of a randomized controlled trial

	Variables	Baseline	Follow-up			Variable type	Objective
		**t = 0** **Months**	**t = 3 Months**	**t = 6 Months**	**t = 12 Months**		
**PARTICIPANT CHARACTERTISTICS**	Socio-labour level	X				QV	Factors that can affect the final result
	Number of working hours	X				CV	
	Changes in glucose-lowering dose within last 3 months		X	X	X	QV	
	Antidiabetic drugs or insulin	X	X	X	X	QV	
	Type of insulin	X	X	X	X	QV	
	Diet	X	X	X	X	QV	
	Change in diet		X	X	X	QV	
**HABITUAL AND OCUPATIONAL SEDENTARY BEHAVIOUR AND PHYSICAL ACTIVITY**	Total sitting time, workday, weekend (ActivPAL3TM)	X	X	X	X	CV	Reduce
	Number of sitting time interruptions workdays, weekend (ActivPAL3TM)	X	X	X	X	CV	Increase
	Sedentary bouts < 20 minutes workdays, weekend (ActivPAL3TM)	X	X	X	X	CV	Reduce long periods of sitting/ increase short periods of sitting
	Sedentary bouts 20–40 minutes workdays, weekend (ActivPAL3TM)	X	X	X	X	CV	
	Sedentary bouts 40–60 minutes workdays, weekend (ActivPAL3TM)	X	X	X	X	CV	
	Sedentary bouts > 60 minutes workdays, weekend (ActivPAL3TM)	X	X	X	X	CV	
	Standing time workdays, weekend (ActivPAL3TM)	X	X	X	X	CV	Reduce
	Activity time workdays, weekend (ActivPAL3TM)	X	X	X	X	CV	Increase
	Light-intensity physical activity workday, weekend (ActivPAL3TM)	X	X	X	X	CV	Increase
	Moderate-to-vigorous physical activity workday, weekend (ActivPAL3TM)	X	X	X	X	CV	Increase
	Sufficiently or insufficiently active (SBPAAT)	X	X	X	X	CV	Increase
	Domain-specific sedentary behaviour (WSQ)	X	X	X	X	CV	Reduce
	Glycaemic index (mg/dl)	X		X	X	CV	Reduce
	HbA1C (%)	X		X	X	CV	Reduce
**LIPID PROFILE**	Total Cholesterol (mg/dl)	X		X	X	CV	Reduce
	HDL (mg/dl)	X		X	X	CV	Increase
	LDL (mg/dl)	X		X	X	CV	Reduce
	Triglycerides (mg/dl)	X		X	X	CV	Reduce
**ANTHROPOMETRIICS**	Weight (Kg)	X	X	X	X	CV	Reduce
	Height (cm)	X	X	X	X	CV	–
	BMI (kg/m^2^)	X	X	X	X	CV	Reduce

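### The main objective has no primary variable or time point, effectiveness is judged comparison by comparison, and the sample size is tied to no endpoint

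*Protocol article*

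**What the plan says.** The Objectives section states that "the main objective of this protocol for a randomized controlled trial is to assess the effectiveness in the short-medium and long term" of the programme on "reducing sedentary behaviour and increasing habitual and work physical activity in office staff with DM2". Clinical, anthropometric, blood-pressure, well-being and work outcomes are labelled secondary. Within the main objective nothing is ranked. The Outcomes section lists eight families and marks none as primary.

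On timing, "The data collection will be carried out at the beginning and at 3, 6 and 12 months using the activPAL3TM device". Table 1 lists twelve rows for sedentary behaviour and physical activity. Ten come from the activPAL and are split by day type, for example the row beginning "Total sitting time, workday, weekend (ActivPAL3TM". The other two are the SBPAAT and WSQ questionnaires. All twelve are marked as continuous and measured at every follow-up.

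The Statistical methods section measures the effect through the continuous variables of Table 1, takes the change from baseline to month t, and tests it one-tailed. Its criterion is: "The intervention has a positive effect if the results of the intervention group are significantly better than those of the control group".

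The Sample size section uses a generic medium effect, d = 0.5. It gives 176 evaluable patients (88 per arm), raised to 220 for 20% loss. No variable or visit is attached to these figures.

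**The concern.** A primary variable and time point define which hypothesis the trial tests. Here the main objective spans two behaviours, habitual and occupational domains, device and self-report measures, and three horizons. The written criterion can be met by any one of these comparisons. Two things follow. The comparison behind the headline conclusion could be chosen after the results are seen, so that conclusion has no controlled error rate. And the stated power of 0.95 describes a single test that is never identified, so it supports no particular claim.

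**Working it through.** **1. The plan's own figure.** For a two-sample comparison of means with d = 0.5, one-sided alpha 0.05 and power 0.95, the normal approximation gives n per arm = 2 × (1.645 + 1.645)² / 0.5² = 86.6, so 87. The noncentral t calculation gives 88 per arm, 176 in total, as stated. Then 176 / 0.80 = 220, as stated. Two-sided 5% (or one-sided 2.5%) would need 105 per arm, 210 in total, which does not fit. The text never gives alpha in words, so one-sided 5% is an inference from 176. The calculation covers exactly one test.

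**2. Counting the main-objective comparisons (Table 1).**
- activPAL: total sitting, interruptions, four bout lengths, standing, activity time, light activity, moderate-to-vigorous activity = 10 rows × 2 day types = 20
- SBPAAT = 1 and WSQ = 1
- 22 variables × 3 visits (3, 6, 12 months) = **66**
- Workday and weekend pooled: 12 × 3 = **36**
- Without SBPAAT, which classifies people as sufficiently or insufficiently active although marked continuous: 21 × 3 = 63

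**3. False positives if the app has no effect, one-sided 5% per test.**
- Expected number: 66 × 0.05 = 3.3; 36 × 0.05 = 1.8
- Chance of at least one, if independent: 1 − 0.95^66 = 0.966; 1 − 0.95^36 = 0.842

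The measures are clearly correlated, and the protocol gives no correlations. The table below simulates multivariate normal test statistics with an assumed correlation of 0.6 between visits and a common assumed correlation between variables:

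| Between-variable correlation | 66 tests | 36 tests |
|---|---|---|
| 0.3 | 72% | 59% |
| 0.5 | 59% | 48% |
| 0.7 | 44% | 37% |

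As an extreme case, if all 66 statistics were equally correlated at 0.9, the chance would still be 17%.

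**4. Adjusting all tests compared with naming one.** Bonferroni over 66 uses alpha = 0.05 / 66 = 0.00076 one-sided. Power at d = 0.5 with 88 per arm drops to 0.54, and restoring 0.95 would take 189 per arm (378 evaluable, 378 / 0.80 ≈ 473 recruited). One named comparison at one-sided 5% keeps power at 0.951 with 88 per arm; at two-sided 5% it is 0.910.

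**The case against.** Several counter-arguments are fair.

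- **The criterion may only describe how one comparison is read.** The Statistical methods section does not say that a single significant variable makes the trial positive. Its example pairs an activity gain with a cholesterol fall, which could be read jointly. This stands in part: a reader might infer an explicit any-of-66 rule, and the text does not state one. But the example is offered only as an illustration, no joint rule is set, and nothing else says when the programme as a whole counts as effective.
- **Error control may sit in an analysis plan or in the additional files, which are not shown.** This stands. The absence of a multiplicity method is not the point. The point is that the protocol fixes a per-comparison criterion while leaving the main objective without a primary comparison.
- **There is some hierarchy.** This stands. A reader might pool every Table 1 outcome into one family of about 114 tests, but the Objectives section labels the clinical, anthropometric, well-being and work outcomes secondary, so that count is not a fair measure of the main claim.
- **Occupational behaviour is measured.** This stands. A reader might infer from the workday and weekend rows of Table 1 that working hours are not separated. The activPAL section says otherwise: "Working and non-working times will be established by using participants’ daily records", and the Outcomes section lists occupational device outcomes.
- **A false claim is not always more likely than not.** This stands. At a between-variable correlation of 0.7 the chance is below one half.

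**Conclusion.** The point holds in this form: the main objective lacks a primary variable and time point, effectiveness is judged separately for each variable and visit, and the sample size belongs to no endpoint. The chance of at least one false positive effect within the main objective lies between 37% and 97% over the counts and correlations in the table and the independent case. The extreme case of 0.9 throughout still gives more than three times 5%. These figures rest on an inferred one-sided 5%, on assumed correlations, and on reading each significant comparison as a claim of effect. They do not show that a false headline is certain, or that the protocol formally declares success on any single result. This should be settled before the arms are compared, because a primary comparison chosen afterwards would not control the error.

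**What to change.** Before unblinding, name one primary variable and one time point that match the app's stated target. An example is activPAL sitting time during working hours, derived from the work-time diary already collected, at 3 months. Test 6 and then 12 months in fixed sequence, each at the full level, stopping at the first non-significant result. State alpha and sidedness explicitly. Reword the effectiveness statement so that it refers to this comparison, and present the sample size as the calculation for it, with a reason why d = 0.5 is plausible for that variable. Report the remaining variables as secondary, with confidence intervals.

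The cost in text is about one paragraph. The cost in substance is that physical activity, which is part of the main objective, and the other variables can no longer establish effectiveness alone. No extra patients are needed if one-sided 5% is kept: power remains 0.95 at d = 0.5 with 88 per arm. If two-sided 5% is adopted, which is a separate decision, the power should be restated as 0.91; restoring 0.95 would take 105 per arm, that is 210 / 0.80 = 262.5, about 263 recruited.
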